### Main exposures

The main exposure of interest is ethnicity, which is likely to be inconsistently recorded across databases. We will primarily assign ethnicity using staff HR records (ESR or SWISS) and registration databases (if not included/missing from HR records). If ethnicity is missing from these databases, linked EHRs will be assessed. Those with ethnicity recorded as ‘not stated’ or with completely missing ethnicity information will be excluded from the main analyses. Ethnicity will be categorised based on ONS groupings (table 2).

**Table 2 T2:** ONS ethnicity groupings

Broad ethnic categories	Ethnic groups
White	English/Welsh/Scottish/Northern Irish/British Irish Gypsy or Irish Traveller Any other White background
Mixed/multiple ethnic groups	White and Black Caribbean White and Black African White and Asian Any other mixed/multiple ethnic background
Asian/Asian British	Indian Pakistani Bangladeshi Chinese Any other Asian background
Black/African/Caribbean/Black British	African Caribbean Any other Black/African/Caribbean background
Other ethnic group	Arab Any other ethnic group

ONS, Office for National Statistics.

A more granular analysis will incorporate subdivisions of ethnicity (particularly within Asian/Asian British category) if a sufficient number of events are observed.

Occupational group (and its interaction with ethnicity) is also of primary interest. We will assign occupation for the main cohort using data recorded on 1 February 2020 from either HR records or data held by the regulating bodies and the following categories informed by version 17.1 of the NHS Occupational Code Manual (*NHS Digital*):

Ambulance staffAdministrations and estates staffHealthcare assistants and other support staffMedical staffDental staffNursing, midwifery and health visiting staffNursing, midwifery and health visiting learnersScientific, therapeutic and technical staffHealthcare sciencesGeneral payments

A more granular analysis will incorporate subdivisions of occupational groups (particularly the Medical staff group) if a sufficient number of events are observed.

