### Predictors

We will investigate and adjust for the following core predictors: age, sex, comorbidities and socioeconomic deprivation. A description of the definitions for these core predictors, and how they will be assessed, is provided in table 4.

**Table 4 T4:** Definitions for core predictors associated with risk of adverse COVID-19 outcomes

Predictor	Definition
Age	A continuous measure of age (in years) at the index date (1 February 2020), calculated using date of birth as recorded in HR or professional registration databases.
Sex	A categorical measure (female/male/other) as recorded in HR or professional registration databases.
Comorbidities	A categorical measure counting the number of comorbidities for each individual (0, 1 or 2 or more) obtained from primary care records and supplemented with secondary care records in analyses conducted in the hospitalised cohort. Comorbidity count will incorporate conditions from the NHS Digital shielded patient list algorithm and others found to be associated with adverse COVID-19 outcomes.
Socioeconomic deprivation	An ordinal measure using quintiles of the Index of Multiple Deprivation (IMD), the official measure of relative deprivation for small areas in each country, based on residential postcode as recorded in HR or professional registration databases. Where residential postcode is not provided workplace postcode will be used as a surrogate.

HR, human resource; NHS, National Health Service.

Elevated body mass index (BMI), obesity and smoking are also considered key predictors for adverse COVID-19 outcomes;^9 23 24^ however, are likely to be missing for large proportions of the identified cohort. Furthermore, missingness in EHR data is unlikely to be random, preventing standard imputation approaches. Thus, BMI and smoking will not be included as independent predictors in the primary study but instead in a sensitivity analysis exploring COVID-19 outcomes within HCWs where this information is available in primary or secondary care medical records, within 24 months prior to the study start date.

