### Missing data

Missing information for ethnicity, occupation, and other predictor variables will be reported and missing data patterns investigated. To improve completeness, we will use information from multiple data sources. Those with completely missing ethnicity information will be excluded from the main analysis. Comorbidity information will be identified using primary care records; thus, absence of comorbidity codes will be interpreted as absence of comorbidity (ie, not missing).

We will report the coverage of each analysis and the number (%) of HCWs included. Sensitivity to the exclusion of missing data will be assessed using multiple imputation methods.

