### Sensitivity and additional analyses

Dependent on the number of HCWs and events captured, we intend to conduct the following additional analyses:

*Incorporating BMI and smoking into broad analysis*: adjust for BMI and smoking in COVID-19 outcome models if recorded by EHRs either during, or in the 24 months prior to, the study period.
*Incorporating grouping by organisation*: incorporate clustering of HCWs within organisations by fitting hierarchical models to account for within organisation correlation and between organisation heterogeneity.
*Granular analysis within the ‘Asian/Asian British’* ethnicity category: investigate differences in COVID-19 outcomes between HCWs with South Asian (Indian, Pakistani and Bangladeshi), East Asian (Chinese) and Other Asian backgrounds.Granular analysis within the “medical staff” occupational group: investigate differences in COVID-19 outcomes between medical and dental subcategories.Subgroup analysis within hospital workers: investigate COVID-19 outcomes in hospital workers and cluster HCWs within hospitals using hierarchical models.
*Subgroup analysis of ancillary workers*: investigate COVID-19 outcomes in ancillary workers through trusts that employ them directly.
*Missing ethnicity*: explore approaches to deal with missing ethnicity information.
*Missing data*: use multiple imputation to assess the robustness of our findings to missing data.

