The broad analysis will examine associations between ethnicity, occupational group and multiple important COVID-19 outcomes in HCWs employed in the UK, while adjusting for core predictors. Using readily available EHR data enables the investigation of complex models of public health resulting in scalable, population-based measurements of disease burden.^33^ However, we foresee a trade-off between the scale and depth of the data, for example, while incorporating professional registration databases captures HCWs in non-NHS sectors, we are unable to identify whether they are actively working (not retired, on parental or long-term sick leave). Thus, a substudy will use detailed NHS HR databases to enable granular analyses of ethnicity, occupation and COVID-19 exposures in those actively working during the pandemic. Additional hypothesis generating analyses will be conducted where interesting results are found, for example if the study identified a higher mortality incidence in a particular ethnic group, a more detailed analysis investigating differences in disease severity by ethnic group could be planned.

Implications regarding the quality of the EHR data have been considered; multiple data sources will be utilised to limit the impact of missing information for the main exposures (ethnicity and occupation) and outcomes (diagnosis, hospitalisation, death). However, ethnicity information is notorious for being poorly recorded in EHR data and the missing information is unlikely to be missing at random. Even after taking steps to limit the impact of missing information, utilising a complete-case analysis approach may still introduce some sampling bias. Sensitivity analyses are planned to account for predictors expected to have high proportions of non-random missingness, such as ethnicity, BMI and smoking status. However, this study will be limited by the subset of COVID-19 cases that are diagnosed and recorded within the EHR data. Many HCWs with SARS-CoV-2 infections will not be diagnosed, with a US study projecting up to 63%.^28^ Indeed, the study will not capture HCWs with mild or asymptomatic infections in settings where tests are restricted to those with symptoms, and results may be vulnerable to collider bias.^31^ Incorporating both suspected and confirmed COVID-19 diagnoses is likely to increase the number of infections captured, though it is also likely to reduce the specificity of diagnosis by incorporating false positive cases.

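### The plan expects ethnicity to be missing non-randomly, but the only check it names is multiple imputation with no non-random form, which can agree with a biased complete-case ratio

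*Protocol article*

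**What the plan says.** All references are to the protocol article.

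- **Missing data:** "Those with completely missing ethnicity information will be excluded from the main analysis". The same section adds: "Sensitivity to the exclusion of missing data will be assessed using multiple imputation methods". No missing-data assumption and no auxiliary variables are given.
- **Sensitivity and additional analyses** has two separate items. The general one will "use multiple imputation to assess the robustness of our findings to missing data". The one on ethnicity will "explore approaches to deal with missing ethnicity information" and names no method.
- **Discussion and limitations:** "ethnicity information is notorious for being poorly recorded in EHR data and the missing information is unlikely to be missing at random". A little later: "Sensitivity analyses are planned to account for predictors expected to have high proportions of non-random missingness, such as ethnicity, BMI and smoking status".
- **Predictors:** "missingness in EHR data is unlikely to be random, preventing standard imputation approaches". This is worded for health-record data in general. It stands in the paragraph that explains why BMI and smoking are left out of the primary models.
- **Main exposures:** ethnicity comes first from staff and registration records. After that, "If ethnicity is missing from these databases, linked EHRs will be assessed".

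**The concern.** Ethnicity is the main exposure, and the main results are complete-case on it. The article suspects that the gaps are non-random and promises analyses that deal with this. The one method it names works, in its standard form, by assuming that the gaps are random given the observed data.

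The back-fill from health records makes the harmful pattern possible. Staff who are diagnosed or admitted may have more records, so recording can depend on outcome. If it also depends on ethnicity, and the two do not act as separate multiplying factors, the ethnic ratios are biased. Imputation and complete-case results could then agree while both were wrong, and a reader could take the agreement as reassurance on the problem the article itself raises.

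**Working it through.** **1. The plan's own figure.** Inputs from Sample size: 1.4 million staff, 6.2% infected, 63% of infections undiagnosed. 1 400 000 × 0.062 = 86 800 (the article gives 86 600). 86 600 × (1 − 0.63) = 32 042 diagnosed cases, as stated. The non-White share is 100% − 79.2% = 20.8%.

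**2. Why missing-at-random imputation returns the complete-case odds ratio.** Let a and b be the non-White and White cases with recorded ethnicity, c and d the corresponding non-cases, and M1 the cases with missing ethnicity. Imputing from the recorded distribution among cases gives
- non-White cases: a + M1·a/(a+b) = a·[1 + M1/(a+b)]
- White cases: b·[1 + M1/(a+b)]

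The bracket cancels, so a/b is unchanged. The same holds for c/d among non-cases. The odds ratio (a/b)/(c/d) is therefore unchanged, whatever caused the gaps.

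**3. When that odds ratio is biased.** Let r be the probability that ethnicity is recorded (N non-White, W White; 1 case, 0 non-case). Then

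complete-case OR = true OR × (rN1/rN0) ÷ (rW1/rW0).

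The second factor is 1 if recording depends on ethnicity alone, on outcome alone, or on the two as separate multiplying factors. It differs from 1 otherwise.

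**4. Illustrations with a true OR of 1.** The missingness rates are assumptions, because the article gives none. N = 1.4 million with 32 042 cases.

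| Missing: White cases / White non-cases / non-White cases / non-White non-cases | OR, complete-case and imputed | SE of log OR | Chance of p<0.05 |
|---|---|---|---|
| 8% / 8% / 12% / 16% | 0.88/0.84 = 1.048 | 0.0148 | 88% |
| 5% / 5% / 8% / 10% | 0.92/0.90 = 1.022 | 0.0145 | 33% |
| 6% / 8% / 12% / 16% | (0.88/0.84)/(0.94/0.92) = 1.025 | 0.0148 | 40% |

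For the first row, the recorded counts are 5865 non-White cases, 23 347 White cases, 239 010 non-White non-cases and 996 749 White non-cases. SE = √(1/5865 + 1/23 347 + 1/239 010 + 1/996 749) = 0.0148, and z = ln(1.048)/0.0148 = 3.15. Simulation with 20 imputations gave 88% and 32% for the first two rows, the same for complete-case and imputed analyses. With 2050 deaths as the outcome, simulated rejection was 9% to 18% across the patterns tried. With uniform missingness it was about 5%.

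**5. A stronger assumed pattern.** Among diagnosed staff, take a death rate of 6.4% in White staff and a true risk ratio of 1.50 (OR 1.55). Recording probabilities are 0.95 for deaths and 0.70 for survivors among non-White staff, and 0.95 and 0.90 among White staff. The OR is 2.00 by both methods; the risk ratio is 1.87 complete-case and 1.88 imputed. A reverse pattern (0.70 and 0.85; 0.95 and 0.90) gives an OR of 1.21 by both.

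**6. What does move.** In a simulated Poisson model with an age covariate (full data 1.48, complete-case 1.82), missing-at-random imputation gave 1.83. Shifting the log-odds of minority ethnicity by 1 in those with missing ethnicity gave 1.65. In the first row of the table, a common shift of 0.5 moves the OR only from 1.048 to 1.043. Shifts of 0.45 in cases and 0.78 in non-cases bring it back to 1.00. So the shifts need to be able to differ by case status.

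**The case against.** Several counter-arguments have force.

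- **The statement that standard imputation is prevented was made in the BMI and smoking paragraph.** A reader might infer that the article says it of ethnicity. It does not. The link comes from the Discussion, which groups ethnicity with BMI and smoking as non-randomly missing. The tension is real, but it is not a flat self-contradiction about ethnicity.
- **The general imputation item has a wider purpose.** Occupation, age, sex or postcode can also be missing, and imputation can correct incidence rates. With outcome-dependent recording in the 6.4% setting, complete-case rates were 11.2% and 7.5%, while imputed and true rates were both 9.6% and 6.4%. This stands, and is a reason to keep the item.
- **Equality with complete case is conditional.** It is exact for the odds ratio when ethnicity is the only incomplete variable and no auxiliaries are used. With a strong auxiliary, imputation moved part of the way (full data 1.51, complete-case 1.89, imputed 1.61); with a weaker one, less (1.48, 1.82, 1.74). Nationality and country of birth in the HR data could serve, but the article does not assign them that role.
- **An article may leave method to a full analysis plan, and imputation methods could include a non-random form.** This is fair as to detail. The point here is narrower: the Discussion promises an analysis for non-random gaps, and the methods sections name only a technique whose standard form does not supply it.
- **The article compares those with and without recorded ethnicity, admits possible bias from complete-case analysis, and stresses effect size over significance.** All true. The rejection rates above therefore matter less than the size of the shift in the ratio.

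**Conclusion.** The point holds in a limited form. The article's stated aim, to account for non-randomly missing ethnicity, has no matching method. Standard missing-at-random imputation from the analysis-model variables, without informative auxiliaries, essentially reproduces the complete-case ethnicity ratios. Its agreement would not show robustness where recording depends jointly on ethnicity and outcome.

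A reader might go further and conclude that the planned ethnic ratios are biased, or that the check must always pass. The documents support neither. Missingness that depends on ethnicity alone leaves the ratios unbiased. Auxiliaries can move the imputed result. Nothing in the article says that agreement will be presented as robustness to non-random gaps.

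The size rests wholly on assumed missingness rates. The milder patterns give an OR of 1.02 to 1.05 when the truth is 1, which is modest; the high rejection rates come mainly from the 1.4 million cohort. The stronger assumed patterns in step 5 show that larger shifts are possible, not that they are likely. The calculations use two ethnic groups and simpler models than those planned.

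**What to change.** 1. Reconcile Predictors, Missing data, Sensitivity and additional analyses, and Discussion and limitations, and state the assumption under which multiple imputation is used.
2. Keep missing-at-random imputation for the other incomplete variables and for incidence rates, and as the zero-shift reference for ethnicity. Add auxiliaries such as nationality and country of birth where HR data hold them.
3. Fill the missing-ethnicity item with delta-adjusted (pattern-mixture) imputation for the main ethnic contrasts. Shift the log-odds of each minority category among those with missing ethnicity, over a stated range, with shifts allowed to differ between cases and non-cases.
4. Report how the effect estimates change across that range, in keeping with the emphasis on effect size. Do not describe agreement between missing-at-random imputation and complete case as robustness to non-random missingness.

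Cost: the range must be chosen and justified, and there is extra programming and run time across ethnic categories, outcomes and countries. Limiting the work to the main contrasts contains this. No new data are needed.

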## Ethics and dissemination

Ethical approval for the UK-REACH programme has been obtained via the expedited HRA COVID-19 processes (REC ref: 20/HRA/4718, IRAS ID: 288316). A complimentary investigation into the ethical and legal implications of linking professional registration and healthcare data was commissioned in a parallel work package, the results of which are contained in a published policy report (https://uk-reach.org/main/publications/). In brief, the report considers how the relevant legal framework applies to UK-REACH, discusses the implications of carrying out large-scale data linkage and analysis in a trusted research environment and highlights the particular ethical issues arising in the context of research on HCWs’ ethnicity and the COVID-19 pandemic. Ultimately, the report provides a framework for using and linking sensitive data in this project in a way that is ethically, legally and socially acceptable. The study outlined in this protocol is being guided by the relevant recommendations made within the policy report framework. All research data will be anonymised via the SAIL Databank before release to researchers. Study results will be submitted for publication in an open access peer-reviewed journals, disseminated through reports to Government and made available on our dedicated website (https://uk-reach.org/).

## Discussion and limitations

As COVID-19 spreads, the number of cases requiring medical intervention will continue. It is crucial to maintain the healthcare system in the UK and control secondary transmission of COVID-19, and measures to identify and protect the HCWs most vulnerable to infection and adverse outcomes must be implemented. However, current COVID-19 risks in HCWs, particularly within those from historically disadvantaged populations, are poorly understood.

Published evidence of COVID-19 outcomes in HCWs are generally from small studies, in single centre or region settings outside the UK, which have not investigated associations with ethnicity.^30^ COVID-19 studies which use observational data from non-random sampling, such as hospital admissions or voluntary participation, may be affected by collider bias.^31^ One such study assesses outcomes using voluntary self-reported data from symptom trackers only,^32^ thus results are at risk of selection bias due to reliance on accurate self-reporting of exposures and outcomes. A recent study assessing risks of hospitalisation in HCWs and household members in Scotland^18^ had insufficient numbers of HCWs from ethnic minority groups to reliably estimate associations between COVID-19 outcomes and ethnicity. This planned study is, to the authors’ knowledge, the first UK-wide study to assess the relationship between ethnicity and COVID-19 outcomes in HCWs. This large study incorporates ambitious linkage of multiple anonymised HR, professional registration and NHS data sets providing UK-wide coverage of clinical and non-clinical HCWs. However, the lack of a single UK-wide database capturing all HCWs actively working limits our ability to identify all HCWs across all regions. We aim to identify non-clinical ancillary staff not directly employed by the NHS by incorporating contracting organisations.

The broad analysis will examine associations between ethnicity, occupational group and multiple important COVID-19 outcomes in HCWs employed in the UK, while adjusting for core predictors. Using readily available EHR data enables the investigation of complex models of public health resulting in scalable, population-based measurements of disease burden.^33^ However, we foresee a trade-off between the scale and depth of the data, for example, while incorporating professional registration databases captures HCWs in non-NHS sectors, we are unable to identify whether they are actively working (not retired, on parental or long-term sick leave). Thus, a substudy will use detailed NHS HR databases to enable granular analyses of ethnicity, occupation and COVID-19 exposures in those actively working during the pandemic. Additional hypothesis generating analyses will be conducted where interesting results are found, for example if the study identified a higher mortality incidence in a particular ethnic group, a more detailed analysis investigating differences in disease severity by ethnic group could be planned.

Implications regarding the quality of the EHR data have been considered; multiple data sources will be utilised to limit the impact of missing information for the main exposures (ethnicity and occupation) and outcomes (diagnosis, hospitalisation, death). However, ethnicity information is notorious for being poorly recorded in EHR data and the missing information is unlikely to be missing at random. Even after taking steps to limit the impact of missing information, utilising a complete-case analysis approach may still introduce some sampling bias. Sensitivity analyses are planned to account for predictors expected to have high proportions of non-random missingness, such as ethnicity, BMI and smoking status. However, this study will be limited by the subset of COVID-19 cases that are diagnosed and recorded within the EHR data. Many HCWs with SARS-CoV-2 infections will not be diagnosed, with a US study projecting up to 63%.^28^ Indeed, the study will not capture HCWs with mild or asymptomatic infections in settings where tests are restricted to those with symptoms, and results may be vulnerable to collider bias.^31^ Incorporating both suspected and confirmed COVID-19 diagnoses is likely to increase the number of infections captured, though it is also likely to reduce the specificity of diagnosis by incorporating false positive cases.

Findings from this study will directly inform evidence-based guidance to protect and address health inequalities in HCWs during the ongoing pandemic.
